## Abstract

**Background:**

Young people with type 1 diabetes experience elevated levels of emotional distress that impact negatively on their diabetes self-care, quality of life, and disease-related morbidity and mortality. While the need is great and clinically significant, a range of structural (eg, service availability), psychological (eg, perceived stigma), and practical (eg, time and lifestyle) barriers mean that a majority of young people do not access the support they need to manage the emotional and behavioral challenges of type 1 diabetes.

**Objective:**

The aim of this study is to examine the effectiveness of a fully-automated cognitive behavior therapy-based mobile phone and Web-based psychotherapeutic intervention (*myCompass*) for reducing mental health symptoms and diabetes-related distress, and improving positive well-being in this vulnerable patient group.

**Methods:**

A two-arm randomized controlled trial will be conducted. Young people with type 1 diabetes and at least mild psychological distress will be recruited via outpatient diabetes centers at three tertiary hospitals in Sydney, Australia, and referred for screening to a study-specific website. Data will be collected entirely online. Participants randomized to the intervention group will use the *myCompass* intervention for 7 weeks, while at the same time a control group will use an active placebo program matched to the intervention on duration, mode of delivery, and interactivity.

**Results:**

The primary outcome will be mental well-being (ie, depression, anxiety, diabetes-related distress, and positive well-being), for which data will be collected at baseline, post-intervention, and after 3 months follow-up. Secondary outcomes will be functional (work and social functioning and diabetes self-care), biochemical measures (HbA1c), and mental health self-efficacy. We aim to recruit 280 people into the study that will be conducted entirely online. Group differences will be analyzed on an intention-to-treat basis using mixed models repeated measures.

**Conclusions:**

We hypothesize that scores on the outcome measures will improve significantly for young people who use the mobile phone and Web-based intervention compared to the control group. *myCompass* is a public health intervention that is broadly available and free to use. If effective, the program has the capacity to provide convenient and accessible evidenced-based care to the large group of young people with type 1 diabetes who do not currently access the psychosocial support they need.

**Trial registration:**

Australian New Zealand Clinical Trials Registry: ACTRN12614000974606; https://www.anzctr.org.au/Trial/Registration/TrialReview.aspx?id=366607 (Archived by WebCite at http://www.webcitation.org/6YGdeT0Dk).

## Introduction

### Background

Type 1 diabetes is one of the most common chronic diseases of childhood [1]. It is a leading cause of global disease burden [2], and prevalence rates are increasing [3,4]. Insulin deficiency, the hallmark feature of type 1 diabetes, requires life-long management of a complex and demanding self-care regimen that aims to optimize glycemic control and prevent the onset of potentially fatal short- (eg, hypoglycemia and diabetic ketoacidosis) and long-term (eg, micro-vascular and macro-vascular disorders, peripheral nerve disease, and blood vessel disease) health complications [1]. How well young people cope with the challenges of type 1 diabetes, while simultaneously negotiating the normal developmental tasks of childhood, adolescence, and the transition to adulthood, has important implications for their overall physical health, psychological well-being, quality of life, and life expectancy [5].

People with type 1 diabetes feel challenged emotionally by the daily hassles, frustrations, and worries that stem from having a serious and chronic medical condition [6], and are at greater risk of common mental health problems, especially depression, than their peers without diabetes [7,8]. This is clinically important because of the links between psychological morbidity and such adverse health outcomes as greater diabetes symptom burden and functional impairment, decreased diabetes self-care, poorer glycemic control, higher rates of diabetes complications, and failure to transition from pediatric to adult diabetes services [9-11]. Even mild (subclinical) emotional distress has been demonstrated in longitudinal studies to predict “worse-than-expected” clinical and psychological outcomes in adulthood for young people with diabetes, including recurrent hospital admissions for diabetic ketoacidosis [12].

A meta-analysis of interventions for clinical and subclinical depression clearly demonstrated the benefits for mental health and diabetes outcomes [13], yet most young people with type 1 diabetes do not receive the psychological support they need to manage the emotional and behavioral challenges of their diabetes [14,15]. Barriers to obtaining psychological support include insufficient providers of mental health services, poor mental health literacy (ie, lack of knowledge of signs and symptoms), the prioritization of physical symptoms in traditional models of diabetes care, and a range of practical constraints (eg, time, lifestyle, and financial) [6]. Furthermore, there is evidence that many young people with type 1 diabetes find it difficult to discuss mental health issues with their health care providers [15], thus delaying and/or avoiding seeking psychosocial support. There is, therefore, considerable opportunity to improve mental and physical health outcomes for young people with type 1 diabetes by increasing access to psychosocial support that reduces geographic, temporal, and financial barriers to access, and offers advantages of user confidentiality and anonymity.

As an important part of the everyday lives of young people [16,17], the Internet has demonstrated its potential to overcome many of the barriers to accessing mental health services [18], evolving as a popular, efficient, and clinically effective means of delivering empirically supported psychological interventions to the public, including people with diabetes [19-22]. Young people report feeling empowered and comfortable exploring sensitive and stigmatized issues online [23], and online resources, including websites, forums, and social networking sites, are increasing in popularity as sources of mental health support [16,17,24]. Surprisingly, however, there is little research examining the efficacy of Internet delivered psychotherapeutic interventions for reducing distress and improving psychological well-being in young people with type 1 diabetes.

### Study Aims and Hypotheses

Our primary hypothesis is that young people with type 1 diabetes who use the *myCompass* program for 7 weeks will report fewer mental health symptoms (depression, anxiety, and diabetes-related distress), and improved positive well-being compared to an active placebo control group. Our secondary hypothesis is that use of *myCompass* will lead to greater functional gains (diabetes self-care, and work and social functioning), and improvements in glycemic control than the comparison intervention.

## Methods

### Study Design

A 2 (conditions) x 3 (time) RCT design is planned. Participants will be randomized to either the *myCompass* intervention or an active placebo intervention, and each group will have full program access for 7 weeks. Outcomes will be assessed at baseline, post-intervention (8 weeks), and three months follow-up (Figure 1).

**Figure 1 figure1:**
[figure not shown]
Study flow chart.

### Participants

#### Recruitment

Participants will be young people with type 1 diabetes recruited via diabetes services at three hospitals in Sydney, Australia: The Sydney Children’s Hospital, Westmead Hospital, and St Vincent’s Hospital. Clinical staff at each service will provide potential participants with written information about the study and an invitation to take part during a routine visit. Information will describe the study and instruct interested individuals to access a study-specific website to complete an online consent form and screening survey.

#### Eligibility

Young people will be eligible for the trial if they are an Australian resident aged between 16-25 years (inclusive), have an email address and Internet access (via mobile phone, and computer or tablet), were diagnosed with type 1 diabetes by a specialist clinician, and have at least mild symptoms of psychological distress. In light of research suggesting that mental health problems (especially those in the subclinical range) in people with diabetes may, in part, reflect disease-specific distress [26], and given calls for routine screening of both general and diabetes-specific distress in diabetes patients [27], a young person will meet our inclusion criteria if they have a mean score of ≥2 on the Diabetes Distress Scale (DDS) [28], and/or a total score of ≥5 on the on the Patient Health Questionnaire (PHQ) [29]. Exclusion criteria include the inability to read English easily, previous use of the *myCompass* intervention, and current psychotic symptoms (total score of ≥2 on the Psychosis Screening Questionnaire (PSQ) [30] (Textbox 1). Screening will be automatically stopped and appropriate feedback provided if any responses indicate ineligibility.

Inclusion and exclusion criteria.CriteriaInclusionConsent to participateAge 16-25 yearsType 1 diabetes, diagnosed by an endocrinologistAccess to an Internet-enabled mobile phone and computer/tabletPatient Health Questionnaire (PHQ-9) score of ≥5 and/or Diabetes Distress Scale score of ≥2ExclusionInability to read English with easePrevious experience with the *myCompass* programPsychotic symptomsNon-residence in Australia

#### Ethical Concerns and Consent

The study protocol has been approved by the Ethics Committee at St Vincent’s Hospital, which is certified by the National Health and Medical Research Council in Australia (HREC/14/SVH/31), and research governance bodies at each of the participating hospitals. The protocol is registered with the Australia and New Zealand Clinical Trials Registry (ACTRN12614000974606).

### Intervention and Control

#### myCompass

The *myCompass* program [31] is a fully-automated public health intervention with no therapist input that can be accessed via any Internet-enabled mobile phone, tablet, or computer (Figure 2). Developed by mental health researchers at the Black Dog Institute, the program assesses users’ self-reported mental health symptoms on registration, and delivers a personalized intervention that provides round-the-clock self-monitoring of moods and behaviors (via mobile phone, tablet, or computer), and access to twelve interactive evidence-based learning modules (via tablet and computer). The modules provide skills training drawn from cognitive behavioral, interpersonal, problem solving, and positive psychology therapies, and cover such topics as solving problems, managing fear and anxiety, tackling unhelpful thinking, dealing with stress and overload, and increasing pleasurable activities. Each module comprises three 10-minute sessions and has practice activities and home-tasks assigned. Users are encouraged to complete at least two modules, either of their own choosing or from recommendations provided on registration.

In addition, users can schedule short message service (SMS) or email reminders to facilitate self-monitoring. Reminders can be used to receive and print graphical feedback about self-monitoring (including contextual information) on mobile phones or computers to monitor change and assist identification of triggers. It is also possible to receive helpful facts, mental health-care tips, or motivational statements by SMS or email. Registering to use the program is free, and users are not billed for the SMSs they receive. A detailed description of the *myCompass* intervention is provided in [name] et al [25].

**Figure 2 figure2:**
[figure not shown]
Screenshot of myCompass.

#### Active Placebo

The comparator intervention will be an Internet-delivered program called *LiveWell* which delivers health information about a range of topics including skin care, mobile phone use, home environment, casual work, healthy food, and relationships. Developed by the research team to match *myCompass* on duration and mode of delivery, the program also contains practice activities, home tasks, and factual SMS messages (sent to participants once-weekly), and a symptom check at 4 weeks, to replicate the interactivity of *myCompass*, but has no therapeutic content.

### Procedure

Participants will have access to the full intervention on their mobile phones and computer devices for 7 weeks. Although participants will be encouraged to use the programs ad libitum during the intervention period, it will be recommended that they complete at least two program modules in their own time. Assessment will be conducted completely online. At each assessment time-point, participants will receive an email asking them to log into the study website to complete the outcome measures. The email sent at 3-months follow-up will also prompt participants to visit their diabetes specialist for assessment of glycosylated haemoglobin (HbA1c).

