### Measures

The assessments that will be completed at baseline, post-treatment, and 3-months follow-up are summarized in Table 1. Demographic data will include gender, age, marital status, highest education level, and whether the young person is currently working and/or studying. Disease-related information will include age at diagnosis, treatment modality, and diabetes complications status. Participants will also nominate their general practitioner (GP) and diabetes specialist in order to facilitate risk management and the collection of HbA1c results by research personnel.

**Table 1 table1:** Measures used at screening, baseline, post intervention, and 3- month follow-up.

Measure	Screening	Baseline	Post-test	3 months
Demographic and disease-related variables		X^a^		
Psychosis Screening Questionnaire (PSQ)	X			
Patient Health Questionnaire-9 (PHQ-9)	X		X	X
Generalized Anxiety Disorder-7 (GAD-7)		X	X	X
Diabetes Distress Scale (DDS)	X		X	X
Warwick-Edinburgh Mental Well-being Scale (WEMWBS)		X	X	X
Work and Social Adjustment Scale (WSAS)		X	X	X
Summary of Diabetes Self-Care Activities (SDSCAS)		X	X	X
Hyperglycemia/Hypoglycemia scale		X	X	X
Glycosylated haemoglobin (HbA1c)		X	X	X
Mental Health Self-Efficacy Scale (MHSES)		X	X	X

^a^The X indicates the time-points at which the specific measure will be administered.

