#### Glycemic Control

The 7-item Hyperglycemia Scale and 7-item Hypoglycemia Scale [46] will be used to assess participants’ self-reports of symptoms associated with high and low blood glucose, respectively. Additionally, as an objective indictor of glycemic control, participants’ HbA1c results will be retrieved from medical records (see Figure 1). The measurement of HbA1c provides an index of glycemic control over the preceding 2-3 months, and is useful for evaluating whether a person has achieved and maintained their treatment targets, as well as estimating their risk of chronic diabetes complications [47].

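### HbA1c is scheduled and tested at post-test, but the article describes no step that yields an 8-week value, and the split alpha departs from the sample-size basis of 3-month change

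*Protocol article*

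**What the plan says.** In the Measures section, the HbA1c row of Table 1 reads "Glycosylated haemoglobin (HbA1c) X X X", the marks standing under baseline, post-test and 3 months. The table's footnote explains: "The X indicates the time-points at which the specific measure will be administered".

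The Procedure section says that assessment is entirely online and that an email at each time point asks participants to log in and complete the measures. It mentions HbA1c once: "The email sent at 3-months follow-up will also prompt participants to visit their diabetes specialist for assessment of glycosylated haemoglobin (HbA1c").

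Under Glycemic Control, "participants’ HbA1c results will be retrieved from medical records (see Figure 1"). The Measures section adds that participants nominate a GP and a diabetes specialist, partly to help with "the collection of HbA1c results by research personnel". Glycemic Control also states: "The measurement of HbA1c provides an index of glycemic control over the preceding 2-3 months".

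The Sample Size section justifies 280 participants (140 per arm) by 80% power for an HbA1c decrease of 0.5%, using an SD of 1.04 for change over 3 months. The Statistical Analysis section applies one rule to outcomes generally: a mixed model with a time-by-condition interaction and, if that is significant, Bonferroni-adjusted group comparisons at post-intervention and at 3 months.

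**The concern.** An online questionnaire cannot produce an HbA1c value; someone has to take a blood sample. A baseline value is plausible because recruitment takes place at a routine clinic visit. A 3-month value has a described prompt. For the 8-week post-test the article describes no test and no prompt, so the post-test mark in Table 1 has no visible source other than tests that happen to be in the record.

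Three things follow.

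- **Selection.** If post-test values exist mainly for those who attended clinic around week 8, attendance may be related to glycemic control, self-care or distress. A mixed model accepts incomplete cases, but it does not remove bias when missingness depends on HbA1c values that were not observed.
- **Timing.** By the article's own description of what HbA1c reflects, an 8-week value may include some control from before randomisation. At the other end, the prompt travels in the 3-month email itself, so a test made in response to it falls after that email.
- **Mismatch with the sample size.** HbA1c is the only objective outcome and the stated reason for recruiting 280 rather than 240. It was sized on one contrast, 3-month change, but would be tested as one of two, at half the alpha.

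**Working it through.** **Inputs from the Sample Size and Statistical Analysis sections:** difference 0.5; SD of change 1.04; power 80%; 140 per arm; attrition 50%; overall level .05, adjusted for two contrasts. Two assumptions are added: tests are two-sided (not stated), and the 50% attrition, which is stated for the self-report calculation, also applies to HbA1c.

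**1. Reproducing the plan's figure.** Standardised difference = 0.5 / 1.04 = 0.481. By the normal approximation, n per arm = 2 × (1.960 + 0.842)² / 0.481² = 67.9, so 68. Dividing by 1 − 0.5 gives 136 per arm, 272 in total. The t-test version gives 68.9, so 69 per arm, 138 after attrition, 276 in total. Both are close to 280. Without attrition, 140 per arm would have about 98% power, so 280 matches the stated 80% only if 50% attrition is applied. That leaves 140 × 0.5 = 70 evaluable per arm.

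**2. Effect of the alpha split on the 3-month contrast.** Two contrasts give .05 / 2 = .025 each. Two-sample t-test power:

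| Evaluable per arm | alpha .05 | alpha .025 | Loss |
|---|---|---|---|
| 70 (50% attrition) | 80.6% | 71.8% | 8.8 points |
| 140 (no attrition) | 98.0% | 96.1% | 1.9 points |

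At .025 with 80% power the t-test needs 83.5, so 84 evaluable per arm: 168 per arm with 50% attrition, 336 in total. These figures ignore the additional requirement of a significant interaction before the contrasts are examined.

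**3. Effect of missing post-test values.** The article gives no expected completeness, so availability is varied as an assumption. The model has a separate mean for each arm and time, equal correlation between times (0.5 to 0.8), change SD 1.04, 70 per arm with baseline and 3-month values, and post-test values missing at random. Power is for a 0.5 difference at .05, by the normal approximation:

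| Share with a post-test value | Post-test contrast | 3-month contrast |
|---|---|---|
| 100% | 81% | 81% |
| 50% | 58–60% | 81% |
| 25% | 36–38% | 81% |
| 10% | 18–19% | 81% |

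The standard error of the 3-month contrast is 0.176 in every row (1.04 × √(2/70) = 0.176). Missing post-test values therefore weaken the post-test contrast, but they cost the 3-month contrast no precision.

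**4. Overlap with the pre-randomisation period.** Two to three months is about 8.7 to 13 weeks. Less the 8 weeks since baseline, that leaves about 0.7 to 5 weeks before randomisation: almost nothing at the short end, a material share at the long end.

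**The case against.** A reader might infer that post-test HbA1c will be sparse, self-selected and uninterpretable. The documents do not support that. They give no testing frequency and no expected completeness. Research personnel retrieve results through named clinicians, and the baseline value also has no described prompt, so the absence of a prompt does not prove the absence of a value. Figure 1, which the article cites for HbA1c retrieval, is not shown and may state the retrieval points. The mixed model is valid if values are missing at random, and no departure from that is demonstrated. Any overlap with the pre-randomisation period affects both randomised arms, so it would dilute the 8-week difference rather than make it meaningless. All of this stands, and limits the point to post-test values that may be incomplete and dependent on attendance.

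A reader might also infer that the missing values cause the loss of power. They do not: the Bonferroni rule applies to every outcome and would cost the same with complete data. Nor is the 8.8-point loss certain. Record-based HbA1c need not suffer the dropout assumed for questionnaires, and with no attrition the loss is about 2 points.

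Finally, a sampling window and the recording of sample dates are details that an article may leave to the full protocol, and their absence is not counted here. What the objection does not remove is the mismatch between Table 1 and the Procedure section, or that between the single contrast used for sizing and the two contrasts tested.

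**Conclusion.** The point holds in a limited form. Table 1 schedules a post-test HbA1c that no step described in the article produces, and the general analysis rule would still test it. The resulting 8-week comparison may be incomplete, may depend on clinic attendance and may partly reflect control before randomisation. How far any of this occurs cannot be established from the article.

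Separately, the contrast that justifies 280 participants would be tested at .025 rather than .05. Power then falls from 80.6% to 71.8% if 50% attrition applies to HbA1c, an assumption, though the one that reproduces 280; it falls from 98.0% to 96.1% if there is no attrition. HbA1c is a secondary outcome, so the conclusions on mental well-being are not affected. The correction is worth making because HbA1c sets the recruitment target and the change is small.

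**What to change.** - **Reconcile Table 1 with the Procedure section.** Either remove the post-test HbA1c mark, or state how an 8-week value is obtained and treat it as descriptive.
- **Name one HbA1c test.** Specify the baseline-adjusted group difference at 3 months, tested at .05, as the single HbA1c comparison, outside the two-contrast Bonferroni set. This matches the analysis to the stated sample-size basis.
- **Move the prompt.** Send the HbA1c reminder ahead of the 3-month date so that samples fall near it.

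The cost is one table cell or one explanatory sentence, a sentence in the analysis section and a change in email timing. No additional participants are needed. The loss is a formal 8-week HbA1c test.

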### Statistical Analysis

Analyses will be completed with SPSS 22 software. Chi-squares (categorical variables) and *t* tests (continuous variables) will be used to compare demographic and disease-related variables and baseline scores on the outcome measures for the intervention and attention control groups. Similar analyses will be performed comparing participants who do (non-dropouts) and do not (dropouts) return completed questionnaires at each of the post-intervention and follow-up assessments to explore possible biases in study attrition.

Outcomes at each time point will be analyzed on an intention-to-treat basis using linear mixed modeling (LMM) [51], with time points as a within-group factor and intervention as a between-group factor. In LMM, incomplete cases are included in the analysis, and all available data is used to obtain parameter estimates. The interaction of time and study condition will be of primary interest in each analysis, with a significant interaction indicating a group difference in the pattern of change over time in the outcome of interest. Significant interactions will be explored using sets of Bonferroni adjusted comparisons of the two groups at post-intervention and 3-month follow-up. All effects will be tested at *P*<.05, with adjustment according to the number of contrasts in each set. Within- and between-group effect sizes will be calculated using Cohen’s d (based on the pooled standard deviation).

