### Limitations

Recruitment of participants through tertiary hospital diabetes outpatient clinics is an obvious limitation of this study, and means that our findings may not generalize to young people with type 1 diabetes managed outside the hospital system. Nevertheless, because it can be difficult to recruit young people into RCTs [55], and given our target sample size of 280, we feel that the proposed recruitment strategy will ensure timely and cost-effective data collection. In addition, recruitment via hospitals will enable us to examine the potential advantages and disadvantages of including the *myCompass* intervention as part of routine specialist care for young people with type 1 diabetes.

Another possible limitation relates to the brevity of the study and the time intervals for measurement. Whereas the proposed assessments (immediately post-intervention and at 3-months follow-up) are sufficient to demonstrate change in the primary and secondary outcome measures, a longer-term follow-up is necessary to determine the consistency of the study findings and the pattern of the effects of the intervention over time. For this reason, consent will be sought from participants at 10 months for a supplementary 12 months follow-up assessment. Separate ethics approvals will be obtained for this part of the study and the data will be analyzed and reported independently of this project.

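### Table 1 schedules HbA1c at the 8-week post-test, but the text shown prompts a test only at 3 months; the 8-week occasion still enters the HbA1c model and one of its two Bonferroni contrasts

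*Protocol article*

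**What the plan says.** - **Schedule.** In the protocol article, Measures, the HbA1c row of Table 1 reads "Glycosylated haemoglobin (HbA1c) X X X": baseline, post-test and 3 months. Study Design fixes the timing: "Outcomes will be assessed at baseline, post-intervention (8 weeks), and three months follow-up".
- **How a value arises.** Procedure says that all assessment is online and that an email goes out at each time-point. Only the last email asks for a blood test: "The email sent at 3-months follow-up will also prompt participants to visit their diabetes specialist for assessment of glycosylated haemoglobin (HbA1c").
- **Source.** Under Glycemic Control, "participants’ HbA1c results will be retrieved from medical records (see Figure 1"). That figure is not in the text available. Measures adds that participants name their diabetes specialist so that research staff can collect results.
- **Analysis.** Statistical Analysis applies one scheme to every outcome: a linear mixed model with the time-by-condition interaction tested at .05. A significant interaction is followed by Bonferroni-adjusted "comparisons of the two groups at post-intervention and 3-month follow-up", with the adjustment set by the number of contrasts in the set.
- **Size.** Sample Size justifies 280 (140 per arm) by 80% power for a 0.5% difference in HbA1c. It uses a standard deviation of 1.04 for change over 3 months.

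**The concern.** Table 1 and the Procedure disagree about whether the study obtains an HbA1c at 8 weeks. A table mark says that it does. The Procedure sends an email at every occasion but adds a test request to only one of them, which suggests that a test was planned at 3 months and not at 8 weeks. No online assessment draws blood, so an 8-week value would exist only if routine care happened to produce one.

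Two things are at stake. First, the HbA1c interaction test would include an occasion whose data depend on who attended clinic around then. Second, if that test is significant, the 8-week comparison takes half of the .05 available to the follow-up contrasts. The 3-month contrast is the one that matches the standard deviation used to size the trial, and it would be left with .025.

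**Working it through.** **Inputs.** From Sample Size: difference 0.5, SD of change 1.04, power 80%, attrition 50%, 140 per arm. From Statistical Analysis: .05 per set and two contrasts. Two-sided testing is assumed, since sidedness is not stated.

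**1. Reproduce 280.** Standardised difference: 0.5/1.04 = 0.481.
- Normal approximation at .05: n per arm = 2 × (1.960 + 0.842)² × (1.04/0.5)² = 2 × 7.85 × 4.33 ≈ 68. That is 136 in total, and 136/0.5 = 272.
- Two-sample t test: 69 per arm, 138 in total, and 138/0.5 = 276.

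Both are within 3% of 280. The match needs one HbA1c contrast at the full .05, and 280 read as the number randomised before 50% attrition. A one-sided test gives 54 per arm, or 108/0.5 = 216, which does not match.

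**2. Alpha per contrast under the plan.** With two contrasts in the HbA1c set, 0.05/2 = .025 each.

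**3. Power of the 3-month contrast (t test).**

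| With data per arm | at .05 | at .025 |
|---|---|---|
| 70 (140 less 50%) | 80.6% | 71.8% |
| 140 (all have a record value) | 98.0% | 96.1% |

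The normal approximation gives 81.2% and 72.7% at 70 per arm. Because the contrasts are run only after a significant interaction, the chance of declaring the 3-month difference cannot exceed these figures.

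**4. Size needed at .025.** 80% power takes about 84 per arm with data (t test): 168 in total, or 168/0.5 = 336 randomised. The normal approximation gives 83 per arm, 166 in total, and 332 randomised.

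**5. The 8-week contrast itself.** The document gives neither the share of participants with a result near week 8 nor a window for accepting one. The shares below are therefore assumptions. Power is for 0.5% at .025 by the normal approximation, borrowing the 3-month SD of 1.04.

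| Assumed share of 140 per arm | n per arm | Power |
|---|---|---|
| 50% | 70 | 73% |
| 40% | 56 | 62% |
| 30% | 42 | 48% |
| 20% | 28 | 33% |
| 10% | 14 | 17% |

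Across this range the 8-week contrast stays below 80%. With complete 8-week data it would reach 96%.

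**The case against.** The strongest reply is that a missing prompt does not prove a missing value. Figure 1 is cited for HbA1c retrieval and cannot be seen. Research staff have a route to results through the nominated specialist. An article may leave sampling logistics to the full protocol. Baseline HbA1c has no prompt either. This stands as a limit on the point: it rests on the text shown. It does not remove the mismatch, because a retrieval route does not produce a test. The baseline case also differs, since recruitment takes place at a routine clinic visit and a nearby record is more plausible then.

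Four stronger readings are tempting, and the document does not support them.

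- **That 8-week values will be sparse and self-selected.** No testing frequency or expected count is given, so this is a possibility only. Bias between arms would further require attendance to relate to outcome differently by arm, or in ways that the model's observed data do not capture.
- **That half of the whole HbA1c error allowance is lost.** The interaction is tested at the full .05. The split applies only to the contrasts that follow a significant interaction.
- **That the plan calls the 8-week assessment alone adequate for HbA1c.** Limitations says that the two assessments ("immediately post-intervention and at 3-months follow-up) are sufficient to demonstrate change in the primary and secondary outcome measures") suffice. It speaks of them together, so that sentence needs no change.
- **That an 8-week HbA1c necessarily reflects time before the program.** Glycemic Control says "The measurement of HbA1c provides an index of glycemic control over the preceding 2-3 months". Eight weeks is close to the lower end of that range, so carry-over arises only towards the upper end.

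The power loss also depends on the reading of 280. Record-based HbA1c need not be lost when a participant stops answering questionnaires, and Sample Size calls 280 the final number. With all 140 per arm the loss is about two percentage points.

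**Conclusion.** The point holds as a visible contradiction between Table 1 and the Procedure that carries through to the HbA1c analysis. On the text shown, the 8-week occasion has no step that generates a value. It nevertheless enters the interaction test and would take one of two follow-up contrasts.

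The cost to the 3-month contrast is about 9 percentage points (80.6% to 71.8%) if 70 per arm have data. That is the reading under which the stated 280 and 80% power reproduce. The cost is negligible (98.0% to 96.1%) if every participant has a record value. HbA1c is a secondary outcome, but it is the one given as the reason for 280, so the plan should say which contrast that number supports. How many 8-week values would exist, and whether they would be selective, cannot be settled from the document.

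**What to change.** Reconcile Table 1 with the Procedure.

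- **If no step obtains an 8-week HbA1c:** remove the post-test mark from the HbA1c row. Model HbA1c at baseline and 3 months only, with one group contrast at .05, and list any 8-week record values descriptively. With two occasions the interaction has one degree of freedom and is itself the group difference in change. This alters wording only and restores the alpha under which 280 reproduces. The cost is that no formal 8-week HbA1c comparison is reported.
- **If an 8-week value is intended:** state in the Procedure how it is obtained and in what window around week 8 a record value counts. Restate the HbA1c power at .025 with the expected number of values at each occasion. On the 50% attrition reading, 80% power at .025 would need about 336 randomised (332 by the normal approximation) in place of 280. The cost is the added collection step, and either a larger sample or a lower stated power.
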